#### Estimation of mood instability

Estimates of instability will be based on readings obtained via the Monsenso system. Relatives and patients score their daily mood on a 9-point scale (patients on a scale from − 3 to + 3 and relatives on a scale 0–8). For each participant, a mood instability measure will be estimated for each day and aggregated in accordance with prior definitions by applying the root mean square successive difference (rMSSD) method [78–80]. The daily mood instability measures, reflecting the extent to which a daily and the previous day’s scores of self-monitored mood differ from one another during follow-up, will be computed as the squared successive difference (SSD) of the reported values. Consequently, daily instability measures can only be computed when consecutive daily values are present. The resulting SSD values are aggregated for each participant as the root mean square successive difference (rMSSD), taking the square root of the mean of the SSD values [80–83]. The instability measures will be computed following the original definition of the rMSSD score. The differences are squared such that positive and negative differences do not cancel out when the values are aggregated by computing the mean. Squaring the values also puts more weight on larger differences. Finally, the square root of the mean puts the aggregated value back on the original scale.

### Interim analyses {21b}

There is no planned interim analysis.

### Methods for additional analyses (e.g., subgroup analyses) {20b}

We plan to conduct an interaction analysis to test the effect of the type of relative (e.g., partner or parent) as well as cohabitation status between patient and relative.

### Methods in analysis to handle protocol non-adherence and any statistical methods to handle missing data {20c}

Missing data will be handled as missing-at-random, and therefore we will not conduct imputations strategies. Non-adherence will be minimized by checking adherence to smartphone-based monitoring continuously.

### Plans to give access to the full protocol, participant-level data, and statistical code {31c}

The datasets analyzed during the current study and statistical code will be made available from the corresponding author on reasonable request after publications from the R-Bipolar study, as is the full protocol.

## Oversight and monitoring

### Composition of the coordinating center and trial steering committee {5d}

[name], Professor, MD, DMSc is the trial sponsor and principal investigator (see affiliation and contact information on the front page). The researcher JRS conducts the study in accordance with the protocol. MV and MFJ helped in developing the protocol and participated in the group that oversees the trial on an ongoing basis. Further, a total of ten relatives of the patients with bipolar disorder were involved and interviewed as part of a qualitative study.

### Composition of the data monitoring committee, its role and reporting structure {21a}

N/A, As this is not a clinical trial of medication, a data monitoring committee is not needed.

### Adverse event reporting and harms {22}

Although psychoeducation is not intended as therapy, there are therapeutic elements and thus also the possibility of adverse events [84]. After the sessions, the participants are asked to complete an online questionnaire that includes evaluation questions, where they can report any negative experiences. Also, parallel to the RCT, JRS performed qualitative interviews with ten participants to get a rich insight into the participants’ experiences with psychoeducation. The results from the qualitative analysis will be published in an independent paper.

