**Fig. 1 Fig1:**
[figure not shown]
Spirit study schedule of enrolment, interventions, and assessments

*Primary outcome*: Daily self-reported mood instability collected via the Monsenso app^1^ [43] for relatives during the period in which the participants are part of the research project.*Secondary outcomes*: Other critically daily self-reported smartphone-based data including daily activity level, anxiety, irritability, stress, cognition, sleep, alcohol consumption, caregiver burden, and medicine as reported in [44].

Clinically rated observer-based scores on the following three scales: Hamilton Depression Scale-6 items (HAM-D6) [45] (being more sensitive in RCTs than the HAM-D17 [46]), the Young Mania Rating Scale (YMRS) [47] and the Functional Assessment Short Test (FAST) (a 24-item interviewer-administered interview concerning autonomy, occupational functioning, cognitive functioning, financial issues, interpersonal relationships and leisure time) [48].

Self-assessed scores on the following questionnaires: Burden Assessment Scale [49], Perceived Criticism Measure [22, 50], Carer Quality of Life [51, 52], Carer-Self-Efficacy [34, 53], Bipolar Knowledge Scale [54], Short Form-12 [55, 56], Brief Symptom Inventory [57], Perceived Stress Scale [58], Mood Disorder Questionnaire [59], Major Depression Inventory [60, 61], Childhood Trauma Questionnaire (CTQ) [62]. When the questionnaires are repeated after the intervention, the.

participants are asked to complete a satisfaction survey on the psychoeducation. The satisfaction survey was developed in close collaboration with the clinicians from the Copenhagen Affective Disorder Clinic.

*Tertiary outcomes*: Automatically smartphone-generated data on physical [63], and social activity [64].

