### Plans to promote participant retention and complete follow-up {18b}

We check weekly to see if the participants remember to record in the Monsenso App. If there is a lack of adherence, we contact participants by phone call or text message, whichever is most suitable in the case. JRS sends emails with a reminder and a link to the questionnaire in Redcap 1 to 2 weeks prior to follow-up interviews, thus increasing adherence. If a participant wishes to leave the study, the date and reason are noted in the primary logbook.

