## Trial status

Recruitment began on April 7th, 2022 and so far (January 5th, 2024) a total of 185 relatives have been included in the trial and 25 have dropped out. Recruitment is expected to be completed at the end of January 2024 and final data gathering will be finished in May 2024.

Protocol version 1.

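### Negative experiences are reported after the course, with no parallel collection in waiting-list relatives, so reported adverse events cannot be compared by randomised arm

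*Protocol article*

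**What the plan says.** The section on adverse events and harms {22} grants that the course has therapeutic elements and so could have adverse effects. It names two sources of information. The first is a form completed once the course is over: "After the sessions, the participants are asked to complete an online questionnaire that includes evaluation questions, where they can report any negative experiences". The second is a set of interviews with ten participants about their experience of the course, which will be reported in a paper of its own.

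Other sections bear on the point:

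- Outcomes {12}: when the questionnaires are repeated after the intervention, "participants are asked to complete a satisfaction survey on the psychoeducation". This is probably the form that {22} means, since timing and content match, but the article does not say so.
- Retention {18b}: "If a participant wishes to leave the study, the date and reason are noted in the primary logbook".
- Adherence {11c}: the final questionnaire asks how many of the six sessions the relative attended.
- Outcomes {12} and statistical methods {20a}: HAM-D6, YMRS, FAST, Major Depression Inventory, Brief Symptom Inventory, Perceived Stress Scale and daily app ratings are secondary outcomes. Mixed models with a fixed group effect are planned for mood instability and other outcomes.
- Trial design {8}: controls wait and are offered the course during the following half year.
- Trial status: by 5 January 2024, "a total of 185 relatives have been included in the trial and 25 have dropped out".

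**The concern.** A randomised comparison is the best tool a trial has for separating harm caused by an intervention from distress that would have occurred anyway. Relatives of patients with bipolar disorder carry a substantial background burden, so that separation matters here. The harms method in {22} does not use the comparison. A form that evaluates the course has nothing to ask a relative who has not yet attended it. Controls may complete it after their own later course, but by then they are no longer controls.

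The timing adds a second weakness. A relative who leaves the study before the end may never be sent the form, and distress caused by the sessions is one possible reason for leaving. What remains is an uncontrolled count of spontaneous reports. That is a thin basis for any statement about harm in a trial meant to inform routine use of the course.

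**Working it through.** The plan states no harms figure to reproduce. The check sets the sections side by side and sizes what can be sized.

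**1. Is there a concurrent control report?** Form in {22}: after the sessions, about the sessions. Interviews in {22}: about experience of the course. Waiting list in {8}: no course during the randomised period. Neither named source yields control-arm reports in that period, and a larger sample would not change this.

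**2. Can the ten interviews fill the gap?** Ten of the 185 included is 10/185 = 5.4%. Suppose interviewees were a random sample of attendees and a harm affects a proportion p of attendees (both assumptions). The chance that at least one interviewee is affected is 1 − (1 − p)^10:

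| p (assumed) | chance of at least one |
|---|---|
| 1% | 10% |
| 5% | 40% |
| 10% | 65% |
| 20% | 89% |

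If none of the ten reported harm, the one-sided 95% upper bound on p would be 1 − 0.05^(1/10) = 25.9%. The interviews can describe harms but cannot bound their frequency usefully, and they have no stated control counterpart.

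**3. How many leavers might the form miss?** Dropout is 25/185 = 13.5%, against the 10% assumed in the sample size section {14}. The split by arm is not given. Assuming equal arms of 185/2 = 92.5, the active-arm share is:

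- none of the 25 in the active arm: 0%
- 12 or 13: 12/92.5 = 13.0% or 13/92.5 = 14.1%
- all 25: 25/92.5 = 27.0%

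The range is too wide to give an understatement of harm, and the article gives no rate of negative experiences to combine with it.

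**4. Do the efficacy comparisons already cover harm?** In part. They compare means. If a fraction w of relatives worsens by a points and the rest improve by b, the mean change is w·a − (1 − w)·b, which is an improvement whenever w < b/(a + b). A worsening minority can sit inside a favourable mean. A proportion worsening, by arm, looks at that tail directly.

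**5. Are the data there?** Baseline ratings at T0 precede allocation {17a}, the scales are planned outcomes {12}, and reasons for leaving are logged {18b}. The visit schedule is in a figure not shown here, so I assume that the scales are repeated in both arms before controls start their course.

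**The case against.** The strongest reply is that the trial observes harm in several ways. The interviews are a second named source. Reasons for leaving the study are recorded. Asking how many sessions were attended makes sense only if partial attenders receive the final questionnaire, so stopping the sessions is not the same as missing the form. Daily ratings of mood, anxiety, stress and burden run throughout participation, and the symptom scales are to be compared between arms. A negative experience of the course has no waiting-list counterpart by definition. The article is also a condensation, and the full protocol may hold more.

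Much of this stands, and it rules out stronger readings that a reader might infer:

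- That the post-course form is the sole source of harms information. The interviews contradict this.
- That early leavers provide nothing. Their reasons are logged, and those who merely skip sessions may well get the form.
- That the trial cannot detect harm from the course. Mean deterioration could appear in the planned comparisons.
- That reported harm is understated by a calculable amount. The 13.5% pools both arms and counts departures from the study, not from the course, and no harm rate is given.

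The reply does not remove the narrower point. Section {22} is the dedicated harms section and states its method. That method includes no control-arm collection, does not draw on the leaving reasons, and designates none of the symptom scales as a harms measure. That course-specific complaints have no control counterpart is a reason to use symptom worsening as the comparative measure.

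**Conclusion.** The point holds in limited form. Reported negative experiences come from a post-course form and ten interviews, with no concurrent collection in waiting-list relatives, so they cannot be compared by arm. Reports from relatives who leave the study early may be missed, and the reasons logged for them are not treated as harms data. The symptom-scale comparisons give indirect evidence on mean worsening only.

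The lack of a control rate follows from the design of the form and does not depend on any assumed figure. The loss from early leaving cannot be quantified: the active-arm share could lie anywhere from 0% to 27.0% if the arms are equal. The conclusion rests on {22} being a fair summary of the full protocol's harms method. It does not threaten the primary analysis. It is a worthwhile and inexpensive improvement to what the trial can say about harm.

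**What to change.** Before results are known, add to {22} that harms will also be assessed by randomised arm, over the control-only period, from data already collected:

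(a) The proportion of relatives who worsen from T0 by a pre-specified threshold on HAM-D6, YMRS, Major Depression Inventory, Brief Symptom Inventory and Perceived Stress Scale, with the between-arm difference and 95% CI. A threshold is needed because counting any rise would largely count noise. The interval should allow for relatives of the same patient, who are allocated together {16a}.

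(b) The logged reasons for leaving, tabulated by arm.

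Describe the evaluation-form results as uncontrolled, and give the number of relatives who were sent the form and who returned it.

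The cost is about one extra table, a threshold to choose for each scale, and tabulation of a logbook that exists. Scores will be missing for those who left before follow-up, which (b) covers only in part. A new negative-experience question for both arms would be a more direct remedy, but final data gathering was due to finish in May 2024, so almost no one could still answer it. It is better kept for a future trial.

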### Frequency and plans for auditing trial conduct {23}

The research team including JRS, LVK, MV, and MFJ met every third month to review trial conduct that was discussed every 6 months with a greater research group consisting of 10–12 members.

### Plans for communicating important protocol amendments to relevant parties (e.g., trial participants, ethical committees) {25}

If substantive protocol amendments are needed, this will be discussed in the research group described in section {5d}: Composition of the coordinating center and trial steering committee {5d}. The principal investigator [name] will be responsible for the final decision, and amendments will be registered at the registration site and in the protocol.

### Dissemination plans {31a}

The findings will be widely disseminated at international conferences and meetings including conferences for the International Society for Bipolar Disorders (ISBD) and in scientific peer-reviewed papers. The research group also plans to host a meeting for all the relatives who have participated to present and discuss the results of the trial.

## Discussion

This protocol describes our currently ongoing randomized controlled trial (RCT) that aims at investigating group-based psychoeducation as an intervention for relatives of individuals diagnosed with bipolar disorder (BD). The study is the first large-scale real-world RCT to focus on a relatively short intervention of psychoeducation (6 sessions of 2 h each) in a large group of relatives (approximately 30 participants per group). With this focus, we wish to test an intervention that is feasible to implement in real-life psychiatric settings with limited budgets and time. It is also the first study to use mood instability in relatives as the primary outcome measure and to investigate whether mood instability and other affective symptoms in patients and relatives covary. It could be considered as limitations, that the trial is not blinded and does not include long-term follow-up.

## Trial status

Recruitment began on April 7th, 2022 and so far (January 5th, 2024) a total of 185 relatives have been included in the trial and 25 have dropped out. Recruitment is expected to be completed at the end of January 2024 and final data gathering will be finished in May 2024.

Protocol version 1.

## Data Availability

Any data required to support the protocol can be supplied on request.
